### Safety measures

At the start of the intervention, participants will receive instructions on how to prevent potential injuries and manage discomfort. For Study 2, safety measures will also include considerations for risks associated with VR use, such as motion sickness and user fatigue. Participants will be encouraged to report any adverse events at any point during the study and to document any difficulties or discomfort experienced during or after the sessions in a questionnaire. These questionnaires will be reviewed weekly by the instructors. Any serious incident (e.g., significant injury or medical event) will be reported immediately to the Principal Investigator and, if necessary, to the institutional ethics committee. The incident will be reviewed to determine necessary protective actions. Participants may discontinue or modify interventions upon request or due to adverse events.

### Confidentiality and data access

Each participant will be assigned a unique alphanumeric code based on their order of inclusion to ensure confidentiality and privacy throughout the study. The Principal Investigator and Project Manager will maintain a confidential record linking each participant to their assigned code. All trial data will be anonymized and stored in a secure university database dedicated to the project, accessible only to authorized members of the research team. Once the database is complete, it will undergo a quality control process to verify its accuracy and integrity.

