### Randomization

In Study 1, an independent researcher will use a software-generated random sequence to allocate participants into three groups at a 1:1:1 ratio for each wave (Fig 3). The randomization list will be securely generated and stored on a university server. While the research team will be aware of the allocation sequence, participants will remain unaware of their group assignment until the intervention. In Study 2, participants will be assigned to one of three intervention groups through sequential cohort assignment based on recruitment order. Potential biases in group composition will be mitigated by monitoring baseline characteristics across groups and adjusting for these in subsequent analyses. Outcome assessors will be blinded to group allocation through the use of coded identifiers to ensure unbiased assessments. To prevent unintentional disclosure, participants will be reminded not to discuss their group allocation during post-intervention assessments. To assess blinding success, outcome assessors will guess participants’ group assignments after the final evaluation. The proportion of correct guesses will be compared to the 33% chance level using a chi-square goodness-of-fit test with one degree of freedom. Data analysts will conduct analyses without access to group allocation information, thereby ensuring the integrity of the results.

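### In Study 2 the participant code follows the same order that sets the arm, so it can reveal the allocation it is meant to mask

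*Protocol article*

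**What the plan says.** The blinding statement in the Randomization section is not limited to one study: "Outcome assessors will be blinded to group allocation through the use of coded identifiers to ensure unbiased assessments". The same section has participants reminded at the post-intervention assessment to keep their group to themselves. It also says that the analysts work without allocation information.

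The only participant code that the article describes is in Confidentiality and data access: "Each participant will be assigned a unique alphanumeric code based on their order of inclusion". That section adds: "The Principal Investigator and Project Manager will maintain a confidential record linking each participant to their assigned code".

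The two studies allocate differently (Randomization section):

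- Study 1: "an independent researcher will use a software-generated random sequence to allocate participants into three groups at a 1:1:1 ratio for each wave". On knowledge of that list: "While the research team will be aware of the allocation sequence".
- Study 2: "participants will be assigned to one of three intervention groups through sequential cohort assignment based on recruitment order".

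Assessors guess each participant's arm after the final evaluation. The check on those guesses is: "The proportion of correct guesses will be compared to the 33% chance level using a chi-square goodness-of-fit test with one degree of freedom".

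**The concern.** A masking label should be unrelated to the arm. In Study 2 the label and the arm are both built from the order in which participants enter, so the label runs parallel to the arm. This is separate from concealment at enrolment, because it affects outcome testing and the coded data file.

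The cognitive domains and global cognition are primary outcomes (Cognitive functions). Several of their component tests in Table 2 depend on an examiner's timing, counting or scoring: Trail Making A and B, the accuracy of the Rey figure drawn from memory, Stroop and verbal fluency. The Study 2 hypotheses predict a different profile for each arm, with cognitive gains for HIFT and psychological gains for MBSR. An assessor who infers the arm therefore also knows the expected direction. The DASS-21 outcomes are questionnaires completed by participants and are not exposed in this way.

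**Working it through.** **Inputs.** Study 2 has 45 participants, 15 per group (Sample size). Study 1 has 177, 59 per group (Sample size). The chance level is 33% (Randomization), which three equal arms reproduce: 15/45 = 59/177 = 1/3. The article gives neither the Study 2 arm order nor the cohort boundaries, so the patterns below are assumptions.

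**Study 2, arm order and boundaries both known.** Let r be the rank of the code, 1 to 45.

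- Three consecutive cohorts of 15: ranks 1–15, 16–30 and 31–45 are the three arms, so 45/45 are inferred.
- Cohorts of 5 within each of three waves: the position within each run of 15 gives the arm, so 45/45.
- Strict rotation: the remainder of r divided by 3 gives the arm, so 45/45.

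**Study 2, arm order known, boundaries uncertain.** Suppose each of the two boundaries is off by −3 to +3 places, all equally likely. The mean error per boundary is (3+2+1+0+1+2+3)/7 = 1.71 participants, so two boundaries misplace 3.43. The expected share correct is (45 − 3.43)/45 = 92%. The worst case is (45 − 6)/45 = 87%.

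**Study 2, one participant's arm known, blocks known, arm order unknown.** The known participant settles one block of 15. The other two blocks can be either way round, so a guess gets all 30 right or none right with equal probability. The expected number correct is 15 + 30 × 1/2 = 30 of 45, or 67%. Under rotation, one known remainder gives the same result.

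**Study 1, code alone.** The arm comes from a random list, so rank does not predict it. In simulation, guessing by rank was right for 33.3% under a random permutation of 59 per arm and for 33.4% under permuted blocks of 3. Both are chance. Matching codes to arms needs the list itself, applied in order of inclusion.

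**The guess test at n = 45** (one guess per participant, no dropout). With k correct, the statistic is (k − 15)²/15 + (k − 15)²/30, and the 5% critical value with one degree of freedom is 3.84.

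- k = 21: 36/15 + 36/30 = 3.6, not rejected.
- k = 22: 49/15 + 49/30 = 4.9, rejected. The threshold is therefore 22/45 = 49%.

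Full decoding would be detected, but only after the scores are recorded. In the one-known-arm case, if the other two blocks are guessed the wrong way round, k = 15 and the statistic is 0. The test then shows nothing, although one whole arm is known.

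**The case against.** - **The identifiers may not be these codes.** The article presents the inclusion-order code as a confidentiality measure and does not say that it is the label assessors see. Form labelling is also a detail that a condensed article may leave out. This stands as a condition on the finding. It does not remove it, because no other code is described.
- **Decoding needs more than the code.** This stands. A reader might infer that one known participant unlocks all of Study 2, or that 45 of 45 follows from the code by itself. Neither is supported: the first gives 30 of 45 in expectation even with known blocks, and the second needs both the arm order and the boundaries.
- **Study 1 is not affected in the same way.** This stands. A reader might extend the finding to all 177 Study 1 participants because the research team knows the sequence. But the order of inclusion does not set the arm there, and the plan says assessors are blinded. The risk arises only if an assessor belongs to the team that knows the list and the list is applied in inclusion order.
- **Coded identifiers are not the only safeguard.** This is correct, because participants are also reminded not to disclose their group. That reminder does nothing about information carried by the code.
- **Random IDs may not be enough.** This stands. Study 2 recruits in three waves (September 2025, December 2025 and February 2026), and testing takes place within two weeks before and after the intervention. If cohorts coincide with waves, the test date hints at the arm whatever the ID.
- **Study 2 is small and preliminary.** This is correct, and it limits the consequence.

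**Conclusion.** The point holds for Study 2, on the assumption that the inclusion-order code is the identifier shown to assessors and analysts. The code then tracks the arm. Up to 45 of 45 arms can be inferred with the arm order and boundaries known, about 92% with boundaries uncertain by 3 places, and 30 of 45 in expectation from one known arm with known blocks, against 33% by chance.

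The documents do not support saying that the blind cannot hold. They show that it can be defeated by someone with knowledge of the cohort pattern. The resulting scoring bias cannot be derived from the documents, and Study 2 is a proof of concept whose findings the Discussion already treats as preliminary. For Study 1 the code alone stays at chance, and what is needed is a clear statement of who may see the sequence.

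**What to change.** 1. In Confidentiality and data access, put randomly generated, non-sequential IDs on the Study 2 assessment forms and in the Study 2 analysis file. The Principal Investigator and Project Manager, who already keep the participant–code record, would hold the link to inclusion order.
2. Withhold recruitment order from Study 2 assessors and analysts and, where possible, cohort and date information too. Random IDs alone do not help if cohorts coincide with calendar waves.
3. In the Randomization section, state that assessors and analysts have no access to the Study 1 allocation sequence. Re-labelling Study 1 forms is not needed.

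The cost is one table of random IDs and a small clerical risk in linking IDs. No extra visits or staff are required.

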### Assessments

Quantitative data will be collected first to assess the effectiveness of the interventions and to explore potential mechanisms of change. Assessments will include psychological, cognitive, physical, and physiological measures, conducted within two weeks before the start of the interventions and within two weeks after their completion. A 12-week follow-up will be conducted through online questionnaires to assess long-term psychological well-being. As part of Study 1, biological data will be collected through fecal samples obtained before and after the interventions.

### Baseline measures

After signing the informed consent form, eligible participants will complete baseline questionnaires. These questionnaires will gather demographic information, including age, relationship status, field of study, university, academic program, academic performance, employment status, socioeconomic status, and health history, as part of the demographics and health history questionnaire. Additional questionnaires will assess cognitive reserve [78], personality traits [79], and participants’ expectations regarding treatment outcomes. To estimate general intelligence, the Vocabulary and Matrix Reasoning subtests from the Wechsler Adult Intelligence Scale–III (Wechsler, 2001) will be included in the baseline neuropsychological evaluation [80].

### Outcome measures

#### Psychological well-being.

Depression, anxiety, and stress will be assessed using the Depression Anxiety Stress Scale (Table 2), with changes in scores serving as the primary outcome measures [81]. Additional aspects of psychological well-being will be evaluated through multiple questionnaires assessing psychological symptoms [82], self-esteem [83], mindfulness [83], self-efficacy [84], and quality of life [85] (Table 2).

**Table 2 pone.0328538.t002:** The proposed assessments of YoungFitT.

Outcome measures	Measure method	Description
**Psychological**		
Psychological Symptoms	90 Symptoms Inventory (90-SCL-R)	Direct scores: 0–4; higher scores reflect more symptomatology.
Self-esteem	Rosenberg Self-Esteem Scale (RSE)	Direct scores: 10–40; higher scores indicate higher self-esteem
Depression, Anxiety, and Stress	Depression, Anxiety, and Stress Scale-21 (DASS-21)	Direct score: 0–126; higher scores represent more global symptoms
Mindfulness	Five-Facet Mindfulness Questionnaire (FFMQ)	Direct scores: 39–195; higher scores reflect more mindfulness levels
Self-efficacy	General Self-Efficacy Scale (GSE)	Direct scores: 10–40; higher scores indicate more self-efficacy
**Cognitive**		
Immediate verbal attention	Direct Digit Span (WAIS-III)	Direct score: 0–9; higher scores indicate better performance
Processing speed	Symbol-Digit Coding (WAIS-III)	Direct score: 0–133; higher scores indicate better performance
Visual attention	Trail Making Test Part A	Time (seconds) to complete the numerical sequence. Direct score; higher scores represent poorer performance
Verbal memory	Rey Auditory Verbal Learning Test	Direct score: 0–75; higher scores reflect better performance
Visual memory	Rey-Osterrieth Complex Figure	Memory drawing accuracy at 3–5 minutes. Direct score: 0–36; higher scores indicate better performance
Executive Function – Flexibility	Trail Making Test Part B	Time (seconds) to complete the alphanumeric sequence. Direct score; higher scores reflect worse performance
Executive Function – Inhibition	Stroop Color and Word Test	Interference score calculated as CW − ((W × C/ (W + C)). Higher scores represent better performance. Negative values indicate poorer performance
Executive Function – Verbal Fluency	Phonetic Fluency: Controlled Oral Word Association Test and Semantic Fluency with “Animal” category	Total words evoked in 60 seconds for each letter (P, M, R) and animals. Direct score; higher scores indicate better performance
Verbal Digit Working Memory	Backward Digit Span (WAIS-III)	Span. direct score: 0–8; higher scores reflect better performance
Verbal Comprehension	Vocabulary subtest (WAIS-III)	Direct score: 0–66; higher scores indicate better performance
**Lifestyle**		
Sleep Quality	Pittsburgh Sleep Quality Index (PSQI)	Direct score: 0–21; lower scores reflect better sleep quality
Physical Activity	International Physical Activity Questionnaire (IPAQ)- Short Form	Total physical measured in MET-min/week. Higher scores indicate more physical activity.
Diet	Mediterranean Diet Assessment Tool (PREDIMED)	Direct score: 0–14; higher scores indicate more adherence to a Mediterranean diet
	93-item Food Frequency Questionnaire (FFQ)	Estimate the usual intake of nutrients and food groups over the past 12 months
	Bristol Stool Form Scale	Classifies stool into 7 types based on form and consistency; indicates gut health
**Physical and Physiological**		
Height	Wall-mounted tape measure	Stand upright, feet flat, heels together, head neutral; in meters (m)
Weight	Digital scale	Stand on the scale without shoes; in kilograms (kg)
Body Mass Index (BMI)	Formula: BMI = weight (kg)/ height (m)^2^	Calculate using weight in kg and height in meters squared
Waist and Hip Circumference	Flexible measuring tape	Measure at the natural waistline and at the widest part of the hips in centimeters (cm)
Waist-to-Hip Ratio (WHR)	Formula: WHR = waist circumference (cm)/ hip circumference (cm)	Calculate using waist and hip circumferences in cm
Aerobic Capacity	Submaximal oxygen consumption test	Estimated VO_2_ based on submaximal step test (ml/kg/min)
Lower Body Muscle Power	Countermovement jump (CMJ)	Velocity and power measured in meters per second (m/s)
Strength of the Hand Flexor Muscles	Han-grip test	Right and left hand grip strength in kilogram-force
Balance	Y-balance test	Composite score of each leg Y Balance (% of leg length). Formula: ((YBALANCE_ANTERIOR + YBALANCE_POSTEROMEDIAL+ YBALANCE_POSTEROLATERAL/ (3 × LEG_LENGTH)) ×100
Flexibility	Sit-and-reach test	Sit with legs extended, reach forward along the measuring scale; in cm
Heart Rate Variability (HRV)	Root mean square of successive differences (RMSSD) method	Measure variation in time between successive heartbeats
Systolic and Diastolic Blood Pressure	Sphygmomanometer	Measure with cuff and pressure gauge; in millimeters of mercury (mmHg)
**Biological**		
Microbiota composition and functionality	16S *rRNA* gene sequencing	Sequence of the V3-V4 16S *rRNA* gene regions and metabolic inference
**Perceived outcomes and qualitative interviews**		
Expectation questionnaire	Assesses perceived effects of the intervention on cognition, well-being, fitness, and quality of life	
Semi-structured interviews	Twelve participants per group will report perceived impact, benefits, and barriers to engagement	
**Usability Virtual Reality System**		
System Usability Scale (SUS)	Direct scores: 0–100; higher scores indicate better usability	

#### Cognitive functions.

The battery tests were grouped into four cognitive domains (Table 2), based on the theoretical framework proposed by Lezak et al. (2012) and Strauss and Spreen (1998). Composite scores for each domain will be derived by converting raw test scores into Z-scores, standardized using the baseline mean and standard deviation. To ensure consistency across assessments, all Z-scores will be referenced to the baseline distribution. Domain-specific composite scores will be calculated by averaging the Z-scores of individual tests within each domain. A global cognitive function score will then be computed by averaging these domain-level composites, providing an overall measure of cognitive performance. Changes in cognitive domains and global cognition will be considered primary outcome measures [86,87].

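### The scoring rule for the primary cognitive composites never aligns direction, so followed literally a faster Trail Making time lowers the composite

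*Protocol article*

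**What the plan says.** The Cognitive functions paragraph under Outcome measures gives the scoring in three steps.

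1. Standardise: "Composite scores for each domain will be derived by converting raw test scores into Z-scores, standardized using the baseline mean and standard deviation".
2. Average within domain: "Domain-specific composite scores will be calculated by averaging the Z-scores of individual tests within each domain".
3. Average across domains: "A global cognitive function score will then be computed by averaging these domain-level composites, providing an overall measure of cognitive performance".

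It then sets the status of these scores: "Changes in cognitive domains and global cognition will be considered primary outcome measures". The tests are said to fall into four domains, with a pointer to Table 2. As shown, that table does not label which test belongs to which domain.

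Table 2 gives a scoring direction for each cognitive test. Trail Making A is "Time (seconds) to complete the numerical sequence. Direct score; higher scores represent poorer performance" and Trail Making B is "Time (seconds) to complete the alphanumeric sequence. Direct score; higher scores reflect worse performance". For every other cognitive row, including the Stroop interference score, higher is better.

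Statistical analyses models the change scores by ANCOVA.

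**The concern.** Averaging Z-scores measures performance only if all components point the same way. Two of the components here point the opposite way, and none of the three steps turns them round. The one consistency measure in the paragraph, referring all Z-scores to the baseline distribution, changes location and scale but not sign.

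Read literally, a student who completes Trail Making faster after the intervention receives a lower Z-score on that test, and this pulls down both the domain composite and the global score. Real gains on the other tests are partly cancelled.

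This matters for the contrasts the trial is built on. The hypotheses predict more cognitive gain with HIFT. The Introduction cites improved reaction times after an online HIFT programme and faster work on a flexibility task after mindfulness training. Gains in speed are what Trail Making would pick up, and what the literal rule would count as losses.

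**Working it through.** **The plan's own figure.** Sample size gives a one-way ANOVA with three groups, f = 0.25, α = 0.05 and power 0.80, leading to N = 159 and critical F 3.054. With df 2 and 156 and noncentrality N·f² = 159 × 0.0625 = 9.94, the noncentral F distribution gives critical F 3.054 and power 0.805. Allowing for 10% dropout, 159/0.9 = 176.7, rounded up to 177. Both figures reproduce, and the scoring point does not alter them.

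**Direction.** This needs no assumption about correlation. Suppose a domain has three tests and only Trail Making A improves, by 0.5 baseline SD. Aligned, the composite changes by +0.5/3 = +0.17. As written, it changes by -0.5/3 = -0.17.

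**Share of a uniform gain that is kept.** Assume m tests in a domain, one of them a Trail Making time, and every test improving by d baseline SDs. Aligned, the composite moves by d. As written, it moves by [(m-1) - 1]·d/m = (m-2)·d/m:

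- m = 3: 1/3 = 33%
- m = 4: 2/4 = 50%
- m = 5: 3/5 = 60%

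**Global score.** Assume four domains: one with three tests including Trail Making A, one with four or five scores including Trail Making B, and two without Trail Making. The share kept is (1/3 + 1/2 + 1 + 1)/4 = 0.71 or (1/3 + 3/5 + 1 + 1)/4 = 0.73.

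**Power.** The lost shift is partly offset because the unaligned composite also has a smaller variance when the tests correlate. Let ρ be a common correlation between tests in the performance direction, for the quantities that are analysed.

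- Aligned variance: V₀ = [1 + (m-1)ρ]/m
- Variance as written: V = [m + ρ((m-2)² - m)]/m²
- Ratio of standardised effects: k = [(m-2)/m]·√(V₀/V)

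Example, m = 3 and ρ = 0.5: V₀ = 2/3, V = (3 - 1)/9 = 2/9, k = (1/3)·√3 = 0.577, so f = 0.25 × 0.577 = 0.144.

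Taking f = 0.25 for the aligned composite and N = 159:

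| Tests in domain | ρ | k | f as written | Power |
|---|---|---|---|---|
| 3 | 0 | 0.333 | 0.083 | 0.14 |
| 3 | 0.5 | 0.577 | 0.144 | 0.35 |
| 4 | 0 | 0.500 | 0.125 | 0.27 |
| 4 | 0.5 | 0.791 | 0.198 | 0.59 |
| 5 | 0 | 0.600 | 0.150 | 0.37 |
| 5 | 0.5 | 0.878 | 0.220 | 0.69 |

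Domain membership, ρ and equal gains on all tests are assumptions; the article gives none of them.

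**The case against.** The strongest reply is that the article is silent on reversal and does not instruct anyone to leave the times unreversed. Aligning direction before averaging is routine, a journal article condenses a fuller document, and Table 2 itself flags both Trail Making parts as running the other way. The stated aim of the global score also implies alignment. A wrongly signed component would probably show itself as a negative correlation with its domain partners.

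Much of this stands. A reader might infer that the analysts will use unreversed times, or that the primary cognitive results will be attenuated. The document does not support that; it shows only what the written rule would produce. What does not stand is the suggestion that scoring has simply been left to another document. The article sets out the algorithm step by step for primary outcomes, and those steps, applied to Table 2's directions, contradict the purpose the paragraph gives for the global score.

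The reply is also right about precision. No single power figure can be defended, because domain membership and correlation are unknown. The sample-size calculation is for a generic three-group comparison and is not tied to any cognitive composite.

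A further inference is tempting. Table 2 has a row for the Vocabulary subtest among the cognitive measures, while Baseline measures says "To estimate general intelligence, the Vocabulary and Matrix Reasoning subtests" are used, and general intelligence is a planned moderator. A reader might conclude that the moderator sits inside the outcome. That would require Vocabulary to be repeated after the intervention or to enter a composite, and the article states neither. Table 2 also lists items that are plainly not change outcomes, such as height and the interviews, so a baseline-only reading is coherent. This is a labelling ambiguity and no more.

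**Conclusion.** The point holds for the rule as written: the primary cognitive composites mix components of opposite direction with no alignment step. The sign of the error for Trail Making A and B is certain under a literal reading and depends on no assumption.

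Its size is conditional on the assumptions set out above. On those, an affected domain loses 40% to 67% of a uniform shift and the global score about 27% to 29%. The power ranges in the table apply only to a composite that would otherwise have had f = 0.25. Other groupings would give other figures; a two-test domain with one Trail Making score would keep (2-2)/2 = 0 of a uniform shift.

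DASS-21, also primary, is untouched, as is any domain without a Trail Making score. Stroop needs no reversal. Data collection, randomisation and sample size are not affected.

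**What to change.** Add one sentence to the Cognitive functions paragraph, after the standardisation step: the Z-scores of Trail Making A and B are multiplied by -1 before averaging, so that higher means better for every component.

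As a separate matter of labelling, Table 2 could note that Vocabulary is a baseline measure of general intelligence and not part of any composite.

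The cost is one sentence, one table note and one line of code. No new data are needed and the sample size stays as it is. Study status and timeline expects data collection to run until June 2026, so on that schedule the change can be recorded before the analysis.

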### Sample size

A power analysis was conducted using G*Power software (version 3.1.9.4) for a one-way ANOVA (fixed effects, omnibus) with three groups. Assuming a medium effect size (f = 0.25), α = 0.05, and a desired power of 0.80, the analysis yielded a required sample size of 159 participants, with a critical F-value of 3.054. To accommodate an expected dropout rate of 10%, the sample size was adjusted using the proportional method, resulting in a final target of 177 participants (59 per group). This adjustment ensures that statistical power remains adequate even if participant attrition occurs. Study 2 will include 45 participants (n = 15 per group) as part of a proof-of-concept trial intended for preliminary exploration. For Study 1, biological samples (fecal) will be collected from a randomly selected subgroup of 90 participants (30 per group) before and after the interventions. Furthermore, a subset of 24 participants (12 from each study) will be selected for the qualitative study using purposive sampling to capture diverse perspectives [67]. The sample size is based on previous studies [56,61,68] and evidence suggesting that qualitative inquiry often reaches data saturation with approximately 12 participants [69].

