### Statistical analyses

Data will be entered into a version-controlled Excel database. Analyses will be conducted using the latest available versions of IBM SPSS Statistics and R. A two-tailed p-value < 0.05 will denote statistical significance, with adjustments for multiple comparisons applied where appropriate. Descriptive statistics (means, standard deviations, medians, ranges, and frequencies) will summarize baseline characteristics overall and by group. We will assess distributional assumptions, including skewness and the presence of outliers. Missing data will be characterized by reporting the percentage of missing values for each variable and by evaluating the most likely mechanisms, classified as missing completely at random (MCAR), missing at random (MAR), or missing not at random (MNAR).

Primary hypotheses will be tested under an intention-to-treat (ITT) framework, including all randomized participants. Analysis of covariance (ANCOVA) will model change scores (post-intervention – baseline) using group, baseline score, and selected covariates as predictors. Sex and age will be included as covariates in all analyses. Additional covariates will be considered from a pool of theoretically relevant candidates if they show a significant and meaningful association with the outcomes. To minimize multicollinearity, we will examine the interrelationships among selected predictors and retain only one variable when substantial overlap is observed. If the omnibus test is significant, we will perform pairwise comparisons within each outcome variable using appropriate corrections for multiple comparisons (e.g., Bonferroni). Assumptions of homogeneity of regression slopes, normality, and homoscedasticity of residuals will be checked. If violated, alternative models (e.g., mixed-effects models for repeated measures) will be considered. Between-group findings will be supplemented by within-group analyses (paired t-tests or Wilcoxon tests, as appropriate).

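### Study 1 names six to eight primary outcomes but specifies no error control across them, and its sample size covers one omnibus test at 0.05

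*Protocol article*

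**What the plan says.** All references are to the protocol article.

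- **Psychological well-being** (Outcome measures): "Depression, anxiety, and stress will be assessed using the Depression Anxiety Stress Scale (Table 2), with changes in scores serving as the primary outcome measures". The plural suggests three scores. The DASS-21 row of Table 2, however, gives a single score from 0 to 126, for which "higher scores represent more global symptoms".
- **Cognitive functions** (Outcome measures): the tests form four domains, each domain composite is a mean of Z-scores, and the global score is the mean of the four composites. Then: "Changes in cognitive domains and global cognition will be considered primary outcome measures".
- **Statistical analyses**: "A two-tailed p-value < 0.05 will denote statistical significance, with adjustments for multiple comparisons applied where appropriate". The primary analysis is an ANCOVA of change scores. After a significant omnibus test, "we will perform pairwise comparisons within each outcome variable using appropriate corrections for multiple comparisons"; Bonferroni is given as an example.
- **Sample size**: a one-way omnibus ANOVA with three groups, f = 0.25 and alpha = 0.05. With "a desired power of 0.80, the analysis yielded a required sample size of 159 participants", a critical F of 3.054 is quoted, and the target is 177 after 10% dropout.

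The article gives no hierarchy, no co-primary rule and no split of alpha across the primary outcomes.

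**The concern.** Three choices do not fit together: a primary set with several members, a specified correction that works only inside each member, and a sample size valid for one member at the full 0.05.

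The within-outcome correction limits false claims about which arms differ on a given outcome. It does nothing about the number of outcomes on which an omnibus test can reach significance by chance. The Study 1 hypotheses predict a different profile for each arm (HIFT more cognitive, MBSR more psychological, QG moderate in both), so a pattern could be claimed from whichever outcomes happened to cross 0.05.

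If the error is instead controlled across the set, each outcome faces a stricter threshold and the 0.80 in Sample size no longer describes the primary analysis. The unsettled DASS-21 count adds to this, because the size of the family cannot be read from the article.

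**Working it through.** **1. Reproduce the plan's figure.** Inputs from Sample size: k = 3 groups, f = 0.25, alpha = 0.05, N = 159. The noncentrality is f² × N = 0.0625 × 159 = 9.94, on 2 and 156 degrees of freedom. The critical F is 3.054 and the power 0.805; N = 156 gives 0.797, so 159 is the smallest multiple of three that reaches 0.80. Dropout: 159 / 0.9 = 176.7, rounded up to 177. All stated figures reproduce.

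**2. Count the primary outcomes.** Cognitive: 4 domains + 1 global = 5. DASS-21: 1 (total) or 3 (scores). The family has 5 + 1 = 6 or 5 + 3 = 8 members.

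**3. Familywise error if each omnibus test is read at 0.05.** For m independent tests it is 1 − 0.95^m: 0.265 for m = 6 and 0.337 for m = 8. Independence cannot hold, because global cognition is the mean of the four domains. I therefore simulated the global null: 20,000 trials, 53 per arm, a one-way ANOVA per outcome, global score = mean of domains, DASS total = sum of the three scores. The article gives no correlations, so all of those below are assumptions.

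| Correlation among DASS scores / among domains / between the two sets | Eight outcomes | Six outcomes |
|---|---|---|
| 0 / 0 / 0 | 0.318 | 0.242 |
| 0.3 / 0.2 / 0 | 0.319 | 0.246 |
| 0.5 / 0.3 / 0.1 | 0.284 | 0.224 |
| 0.6 / 0.3 / 0.1 | 0.282 | 0.225 |
| 0.7 / 0.5 / 0.1 | 0.250 | 0.199 |
| 0.7 / 0.5 / 0.3 | 0.246 | 0.198 |
| 0.8 / 0.6 / 0.3 | 0.230 | 0.190 |

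The range is about 23-32% with eight outcomes and 19-25% with six.

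**4. Power per outcome at N = 159 once the family is controlled.** Holm's first and strictest step tests at 0.05/m: 0.05/6 = 0.00833 or 0.05/8 = 0.00625. The first power column uses the plan's ANOVA model. The second credits the planned ANCOVA with an assumed baseline-post correlation r = 0.5, so that f² becomes 0.0625 / (1 − 0.25) = 0.0833 and the noncentrality 13.25.

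| Alpha | ANOVA, as in the plan | ANCOVA, r = 0.5 assumed |
|---|---|---|
| 0.05 (one outcome) | 0.80 | 0.91 |
| 0.025 (two outcomes) | 0.72 | 0.85 |
| 0.05/6 | 0.57 | 0.74 |
| 0.05/8 | 0.53 | 0.71 |

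These are floors for a single outcome with f = 0.25. Later Holm steps use larger alphas, so an outcome reached after other rejections is tested with more power than shown.

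**The case against.** **The general clause.** Statistical analyses attaches multiplicity adjustment, where appropriate, to the 0.05 threshold. A reader might infer that the plan commits to leaving the primary outcomes uncorrected; the text does not say that. What stands is narrower: the clause names neither a family nor a method, and the only correction given any content is within an outcome. A separate analysis plan may supply the rule, but the power figure in Sample size would still describe one test at 0.05.

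**The count and the error rate.** A reader might take eight as the minimum, or quote 34% as the error. Neither is supported. Eight is the upper count, because Table 2 allows a single DASS-21 score, and 34% needs an independence that the definition of global cognition rules out.

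**No rule that one success suffices.** The article does not say that significance on any one outcome makes the trial positive, and its hypotheses describe profiles. This is fair: the familywise figure is the chance of at least one false primary finding, not of a false verdict on the whole trial. It still matters, because each such finding would be reported as primary.

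**The within-outcome Bonferroni.** With three arms, unadjusted pairwise tests after a significant omnibus test already form a closed procedure, so one might call the Bonferroni correction misplaced. It is valid, conservative and offered only as an example. Replacing it is an efficiency preference, not an error to correct.

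**Conclusion.** The point holds in a limited form. Study 1 has six to eight primary outcomes, the scope of adjustment across them is undefined, and the sample size covers one omnibus test. If only the specified steps are followed, the chance of at least one false primary result is roughly 19-32%, about four to six times the nominal 5%. That range depends on the assumed correlations and on whether the DASS-21 counts once or three times.

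The 0.80 power is correct for what it describes, but it does not carry over to the primary set once the error is controlled: 0.53-0.57 at the strictest step under the plan's own model, or 0.71-0.74 if r = 0.5 is assumed. The baseline-adjustment gain must be credited to every option or to none; comparing 0.53 for eight outcomes with 0.85 for two would mix the two models.

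**What to change.** 1. In Psychological well-being and Table 2, state whether the primary DASS-21 outcome is one total or three scores.
2. In Statistical analyses, state that Holm is applied across the omnibus tests of all named primary outcomes at an overall two-sided 0.05. Fix this before any outcome is analysed by group. The within-outcome pairwise correction can stay as it is.
3. In Sample size, state that 0.80 power (N = 159, f = 0.25) is for one outcome at 0.05, and that at the strictest Holm step it is 0.57 with six outcomes or 0.53 with eight (0.74 or 0.71 with ANCOVA and an assumed baseline-post correlation of 0.5).

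The cost is wording in the protocol and registry and a lower stated power per outcome. No endpoint is demoted and no participants are added.

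The investigators could instead limit the primary set to DASS-21 total and global cognition, which gives power 0.72 at alpha 0.025 (0.85 with r = 0.5). That is a larger step: the trial is registered and recruitment began in February 2024, so demoting named primary outcomes could look like outcome switching. It is a trade-off for the investigators, and if chosen it must be recorded as a dated amendment.
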